### **8.2.3 Safety**

The reported adverse events (including local reactions) will be coded according to MedDRA terminology. The number and percentages of subjects with at least one adverse event, and the relationship will be tabulated. Occurrence of particular adverse events (by body system and preferred MedDRA term) and their severity and relationship will be summarized using counts and percentages of subjects.

The erythema and pustular eruption scores with 4 categories will be summarized by treatment regime group and time point using count and percent.

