## **3. INVESTIGATIONAL TRIAL DESIGN**

### **3.1 Study Endpoint(s)**

The primary endpoint will be lesions cure rate and cosmetic outcome by treatment regime 1 compared to lesions cure rate by treatment regime 2, assessed 36 months after PDT. The number of lesion in need of a re-treatment 3 months following the first treatment session in regime 1 will be reported. Clinical suspected recurrences are confirmed by histology. Lesion response rate is defined as number of lesions in complete response at 12 and 36 months of follow-up. We will report on adverse events occurring in relation to both treatment regimes from start of treatment to 3 months following last treatment. We will report on lesion recurrences among lesions treated with either regime 12 and 36 months after PDT. Cosmetic outcome will be determined by clinical assessment (visual inspection and palpation) 12 and 36 months after treatment. The results will be recorded on a 4-point ordinal scale as either excellent (absence of any stigmata other than scar formation after diagnostic punch biopsy), good (slight presence of fibrosis, atrophy or change of pigmentation), fair (moderate presence of fibrosis, atrophy or change of pigmentation) or poor (marked presence of fibrosis, atrophy or change of pigmentation).

The secondary endpoint will be to investigate relationship between clinical and pathological tumour characteristics and tumour recurrences rates, tumour thickness, histopathological BCC subtypes and immunohistochemical markers. Recurrence rate defined both as "raw" (total number of recurrences divided by the total number of tumours treated) and "strict recurrence rate" (total number of patients with recurrence divided by number of lesions observed for at least 36 month) will be reported.

Recurrence rate in relation to BCC subgroup analyses including clinical (superficial or nodular tumour), tumour size and histological characteristics will also be reported. BCC will on the basis of histological growth pattern be divided into two main types (aggressive or non-aggressive type). Tumours will additionally be studied with various immunohistochemical markers for expression of cell proliferation, invasiveness, vascularisation and growth factors.

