## 4. Patient and lesion selection

### 4.1 Number of lesions

277 patients with 374 lesions will be included.

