## **5.2 Randomisation and Emergency Code**

Lesions will be randomized to treatment regime 1 or 2 after treatment by light. In case of multiple BCC, the investigator will number the lesions. The first lesion will be randomized and the next lesion will get the other regime, implying that every second lesion is randomized. The coordinating investigator will supply the randomization code. This is an open study and no emergency code will be required.

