### **8.2.1 Disposition of Lesions**

The number of lesions which are included into the study, which receive Metvix® cream, which are included in safety and/or efficacy evaluation, and which complete each phase of the study, as well as withdrawals will be summarized using counts and percentages of lesions.

Each lesion will be identified, randomized, treated and followed up individually. Patient identification will be recorded anonymously, to account for potential individual susceptibility with respect to response.

The primary outcome is defined as “cure” or “no cure” of a lesion at 3 years, i.e. a binary variable. From previous experience it is expected that the reference treatment leads to a probability of cure of 80 %.

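### Section 8.2.3 counts adverse events by subject although regimes are assigned by lesion, so for multi-lesion patients its tables do not give the by-regime report that 3.1 promises

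*Protocol*

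**What the plan says.** The relevant statements are all in the protocol.

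- **Promise.** Section 3.1: "We will report on adverse events occurring in relation to both treatment regimes", over the period from start of treatment to three months after the last treatment.
- **Unit of assignment.** Section 8.2.1: "Each lesion will be identified, randomized, treated and followed up individually". Section 5.2, on patients with several lesions: "The first lesion will be randomized and the next lesion will get the other regime, implying that every second lesion is randomized".
- **Unit of the safety tables.** Section 8.2.3: "The number and percentages of subjects with at least one adverse event, and the relationship will be tabulated". Particular events, with their severity and relationship, "will be summarized using counts and percentages of subjects". The section states that local reactions are among the coded events, and it names no split by regime for them.
- **Exception.** Section 8.2.3 also says: "The erythema and pustular eruption scores with 4 categories will be summarized by treatment regime group and time point using count and percent".
- **Data capture.** Sections 7.2.3 and 7.2.6 locate an event only as inside or outside the treatment area. Section 5.3 has each lesion numbered and recorded in the CRF, but no section links an adverse event to that number.
- **Size.** Section 4.1: "277 patients with 374 lesions will be included".

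**The concern.** The safety tables use a unit that does not carry the treatment. In a patient with one lesion, subject and regime coincide. In a patient with several lesions they do not, because the patient is exposed to both regimes. A table of subjects then has two simple layouts. It can be pooled over regimes, which gives no comparison, or it can enter the same patient under both regimes, which draws the two columns together.

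The lesion is also the natural unit for most of what will be observed. Section 10.3 describes local effects and does not expect systemic ones. Pain is the first local phototoxic reaction named in 7.2.2, yet it has no summary by regime. What is at stake is the descriptive safety comparison. Section 1.2 names a reduction in side effects among the hoped-for advantages of the simpler regime, and readers will look to these tables to judge that.

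**Working it through.** The protocol states no figure for this overlap, so there is none to reproduce. The check has three steps.

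**1. Does every multi-lesion patient receive both regimes?** By 5.2, lesion 1 is randomised and lesion 2 gets the other regime. Any patient with at least two lesions therefore has at least one lesion in each regime.

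**2. How many patients is that?** Inputs from 4.1: 277 patients and 374 lesions.

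- Mean lesions per patient: 374 / 277 = 1.35.
- Lesions beyond one per patient: 374 − 277 = 97.
- If every multi-lesion patient has exactly *m* lesions, the number of such patients is 97 / (*m* − 1). The value of *m* is an assumption, since the protocol gives no distribution.

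| *m* (assumed) | Patients in both regimes | Share of 277 | Their lesions | Share of 374 |
|---|---|---|---|---|
| 2 | 97 | 35.0% | 194 | 51.9% |
| 3 | 48.5 | 17.5% | 145.5 | 38.9% |
| 4 | 32.3 | 11.7% | 129.3 | 34.6% |

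The first row is the maximum, because each multi-lesion patient uses up at least one of the 97 extra lesions. At least 277 − 97 = 180 patients (65%) therefore have one lesion and one regime.

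**3. What would happen if these patients were entered under both regimes?** Suppose that single-lesion patients split equally between regimes, and that each dual-exposure patient adds the same events to both columns. The dual patients then cancel from the difference in counts but stay in both denominators. The difference seen among single-lesion patients is multiplied by (single-lesion patients per column) / (all patients per column):

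- *m* = 2: 90 / (90 + 97) = 90 / 187 = 48%.
- *m* = 3: 114.25 / (114.25 + 48.5) = 114.25 / 162.75 = 70%.
- *m* = 4: 122.3 / (122.3 + 32.3) = 122.3 / 154.7 = 79%.

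These factors do not depend on the event rates. They apply only to this layout, which the protocol neither prescribes nor excludes.

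**The case against.** A reader might infer that a by-regime report of adverse events cannot be obtained at all. The documents do not support that.

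- Section 8.2.3 already plans the erythema and pustular eruption scores by regime.
- At least 180 patients belong to one regime only.
- Lesions are numbered in the CRF (5.3). The CRF itself is not shown, so its adverse-event page may carry the number.
- Timing helps. Randomisation follows the first illumination (3.3, 5.2), so events up to that point are not specific to a regime. The regimes differ in the second session: at one week in regime 2, and at three months for non-complete responders in regime 1 (5.4). Start dates and onset relative to treatment stage are recorded (7.2.3, 7.2.7). An event in the treatment area during one of those later sessions can be placed; some events of later onset cannot.

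A reader might also infer that the planned analysis biases the difference towards zero. That follows only if the same event is entered under both regimes, and 8.2.3 does not say that it will be. Nor does the protocol promise a test of side effects. Sections 2.1 and 2.2 state no safety hypothesis, and 3.1 promises a descriptive report.

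Finally, column layout and the handling of mixed exposure are commonly left to an analysis plan, and counting subjects is a usual convention.

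All of this stands as a limit on the point, but it does not remove it. The protocol is not silent on the unit: it fixes subjects, for local reactions too, in a trial that assigns regimes by lesion. The location that it requires, inside or outside the treatment area, does not separate two treated lesions in one patient. If data are collected to that text, a later analysis plan can recover the regime only in part.

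**Conclusion.** The mismatch is real and worth correcting. As written, the subject-level tables in 8.2.3 do not deliver the report promised in 3.1 for patients with more than one lesion, except for the erythema and pustular eruption scores. At most 97 of 277 patients (35%) are concerned, and fewer if multi-lesion patients tend to have more than two lesions each. These shares assume that the planned numbers in 4.1 are met and that multi-lesion patients all have the same number of lesions. The dilution factors of 48% to 79% are conditional on double entry and on an equal split of single-lesion patients.

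The only events that cannot be attributed to a regime in principle are non-local ones in multi-lesion patients. The finding concerns descriptive safety reporting and leaves the primary non-inferiority conclusion untouched.

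**What to change.** 1. In 7.2.6 and on the adverse-event page of the CRF, require the existing lesion number with each treatment-area event.
2. In 8.2.3, tabulate local events, including pain, by lesion and regime. Use the lesions treated under that regime as denominator, and allow for clustering of lesions within patient in any interval or comparison.
3. Keep subject-level tables for events outside the treatment area, split by exposure: regime 1 only, regime 2 only, and both.

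The cost is one CRF field, if it is not already there, together with reworded text and some extra tabulation. Sample size and the primary analysis do not change.

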## **8.3 Justification of Sample Size**

The cure rate at 3 years with conventional treatment (5, 6) is expected to be 85 %. The study aims to detect an experimental success rate that is less than 75 % (i.e. a non-inferiority margin of 10 %). With a significance level of 5% and a power of 80% a sample size of 170 lesions per group is required (ref StatExact 8, Cytel Corp. USA). To accommodate some loss to follow-up, we aim to recruit a total of 187 lesions in each group.

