## Statistics

Simple tabulation as well as logistic regression with lesion recurrence (yes/no, a binary variable) at 3 years will be employed to analyze the outcome. As one patient may yield more than one lesion, a mixed effects model with patient identity as random factor will be considered. Different lesions within the same patient will be subject to stratified randomization. The expected cure rate at 3 years (reference) is set to 80 %. The study aims to detect an experimental success rate of no less than 70 % (the non-inferiority margin 10 %). With a sample size of 170 lesions per group, a difference between the two treatment regime groups of at least 10% can be found with a significance level of 5% and a power of 80%.

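### The reference 3-year cure rate is 80% in two places and 85% in the sample-size section; 170 lesions per group gives 80% power only at 85%.

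*Protocol*

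**What the plan says.** Three places in the protocol give the expected 3-year cure rate under the reference regime.

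- **Synopsis, Statistics:** "The expected cure rate at 3 years (reference) is set to 80" per cent. The floor follows: "The study aims to detect an experimental success rate of no less than 70 % (the non-inferiority margin 10" per cent). Then: "With a sample size of 170 lesions per group, a difference between the two treatment regime groups of at least 10% can be found". The level and power stated for this are 5% and 80%.
- **Section 8.2.1, in the paragraph defining the primary outcome:** "it is expected that the reference treatment leads to a probability of cure of 80" per cent. No sample size or power is given there.
- **Section 8.3:** "The cure rate at 3 years with conventional treatment (5, 6) is expected to be 85" per cent. The matching floor is "an experimental success rate that is less than 75 % (i.e. a non-inferiority margin of 10" per cent), and "With a significance level of 5% and a power of 80% a sample size of 170 lesions per group is required". Recruitment is then raised to 187 per group to allow for loss to follow-up.

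Section 8.2.2 tests non-inferiority on the difference in response rates with a margin of 0.1, and plans a two-sided 95% confidence interval for that difference. The 5% level in the synopsis and in 8.3 is not labelled one-sided or two-sided.

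**The concern.** All three statements concern the same quantity, yet they form two complete and different sets of planning assumptions: 80% with a floor of 70%, and 85% with a floor of 75%. Both sets carry the same sample size, level, margin and power. With a fixed margin on the difference scale, the number of lesions needed is proportional to p(1-p), so moving the rate from 85% to 80% must raise the number or lower the power.

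At stake is the chance that the trial misses a simplified regime that is truly as good as the standard one. If power is below the stated 80%, a failure to show non-inferiority is likelier than the reader of the synopsis is told.

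**Working it through.** **Inputs from the protocol.** Reference rate p = 0.80 (synopsis, 8.2.1) or 0.85 (8.3); margin δ = 0.10 (synopsis, 8.2.2, 8.3); 170 evaluable and 187 recruited lesions per group, allocated 1:1.

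**Assumptions not in the protocol.** The true cure rates are equal in the two regimes, and lesions are independent. Because the 5% level has no stated side, both readings are shown: one-sided 5% (z = 1.645), and one-sided 2.5% (z = 1.960), which corresponds to the two-sided 95% interval in 8.2.2. For 80% power, z = 0.842.

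**Formulas.**

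- Required n per group = (z_α + z_β)² × 2p(1-p) / δ²
- Power = Φ(δ / √(2p(1-p)/n) − z_α)

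**Step 1: reproduce the figure in 8.3 (p = 0.85).**

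- Required n, one-sided 5%: 2.4865² × 0.255 / 0.01 = 157.7, so 158.
- Power at 170: the standard error is √(0.255/170) = 0.03873; 0.10/0.03873 = 2.582; Φ(2.582 − 1.645) = 82.6%.
- The Farrington-Manning score formula gives 163 per group. An exact unconditional score test gives 81.3% power at 170 and crosses 80% at about 164 to 168.

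So 170 is a reasonable figure for an 85% rate with a one-sided 5% test, especially from exact software, which 8.3 cites.

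**Step 2: repeat at the rate in the synopsis and 8.2.1 (p = 0.80).**

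- Required n, one-sided 5%: 2.4865² × 0.32 / 0.01 = 197.8, so 198 (Farrington-Manning: 201).
- Power at 170: the standard error is √(0.32/170) = 0.04339; 0.10/0.04339 = 2.305; Φ(2.305 − 1.645) = 74.5%. Farrington-Manning gives 74.1% and the exact unconditional score test 73.6%.
- Power at 187, with no loss at all: √(0.32/187) = 0.04137; 0.10/0.04137 = 2.417; Φ(2.417 − 1.645) = 78.0%.

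**Step 3: both rates, both readings of 5% (normal approximation).**

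| Rate | Level | n for 80% power | Power at 170 | Power at 187 |
|---|---|---|---|---|
| 85% | one-sided 5% | 158 | 82.6% | 85.6% |
| 80% | one-sided 5% | 198 | 74.5% | 78.0% |
| 85% | one-sided 2.5% | 201 | 73.3% | 77.3% |
| 80% | one-sided 2.5% | 252 | 63.5% | 67.6% |

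Exact binomial enumeration of the Wald rule at n = 170 agrees: 74.6% and 82.6% at one-sided 5%, and 63.6% and 73.1% at one-sided 2.5%.

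**Step 4: other readings of the synopsis.** Its sentence about finding a difference of at least 10% could be taken as a superiority calculation, 80% against 70%. The pooled-variance formula then needs 231 per group one-sided or 294 two-sided. None of the methods tried gives 80% power with 170 per group at an 80% rate.

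**The case against.** The strongest reply has four parts.

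1. **The decision rule does not change.** Section 8.2.2 tests the difference against a margin of 0.1 whichever rate is assumed. The 70% and 75% floors are just the assumed rate minus the margin. This is right: the conflict affects planning and power, not how non-inferiority is judged.

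2. **Section 8.3 is sound on its own terms.** It is the formal justification, and 170 does reproduce at 85% with a one-sided 5% test. This also stands, but it does not show which rate is intended. The 80% figure is no slip of one digit: it appears twice, and the synopsis pairs it with a consistent 70% floor.

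3. **The figures for the two-sided 95% interval mix in another problem.** At one-sided 2.5%, 170 falls short at both rates. Fair: the shortfall due to the 80/85 conflict alone is the one-sided 5% figure, about 5 to 6 points of power.

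4. **Lesions are not independent.** Section 5.2 gives a patient's next lesion the other regime, and section 4.1 plans 374 lesions in 277 patients. Positive correlation within patients could therefore reduce the variance of the difference. As an illustration, suppose the 374 − 277 = 97 extra lesions make 97 two-lesion patients, and the same paired share, 97/187 = 0.519, holds at n = 170. The standard error is then multiplied by √(1 − 0.519ρ). At an 80% rate and one-sided 5%, power is about 76.5%, 78.5% and 80.6% for a within-patient correlation ρ of 0.1, 0.2 and 0.3, if the analysis uses the pairing. If it ignores the pairing, power stays at about 75% to 76%. The protocol gives no correlation, says only that a mixed model will be considered, and takes no credit for pairing in its calculation. This limits the precision of the 75% figure but does not support the claim as written.

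**Conclusion.** The concern holds. The protocol contradicts itself on the reference cure rate, and nothing in it reconciles the two values. On the most lenient reading (one-sided 5%, equal true rates, independent lesions), 170 lesions per group gives about 74% to 75% power at the 80% rate, against the 80% claimed. The chance of missing a truly equivalent regime is then about 25% or slightly more instead of 20%. Recruiting 187 per group does not close the gap even with no loss. Judged by the two-sided 95% interval, power at the 80% rate is about 63% to 64%, though part of that shortfall would remain at 85%. The synopsis's power statement for the primary hypothesis is wrong at its own rate and must be corrected.

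**What to change.** Choose one reference cure rate and use it, with its matching floor, in the synopsis, 8.2.1 and 8.3. Restate the power of 170 per group at that rate, and say whether the 5% is one-sided or two-sided, since the figure depends on it.

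- **If 80% is kept:** set the floor in 8.3 to 70%, delete the 80% power claim in both places, and give the actual figure (about 75% at one-sided 5%; about 64% if judged by the two-sided 95% interval).
- **If 85% is kept:** correct the synopsis and 8.2.1, set the synopsis floor to 75%, and add one sentence to 8.3 giving the power should the true rate be 80%.

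The cost is wording in three places. Endpoint, margin, hypothesis and enrolment stay as they are. The only price is a less favourable power statement if 80% is kept.

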### **8.2 Statistical Analysis**

The statistical analysis is the responsibility of [name], Unit for applied clinical research, Faculty of Medicine, Norwegian University of Science and Technology (NTNU),

Clinical Study Protocol  
Version: Final revised  
Date: 2012-03-27

Sponsor: NTNU  
Study Code: NTNU 2011-1  
EudraCT No: 2011-004797-28 NO 20120327

Trondheim, Norway. Tabulation of summary statistics and data analyses will be performed using SPSS® software (PASW for Windows version 17.0 (PASW Inc)). The primary presentation and analysis will be based on data pooled across centres. Relevant summaries of data for individual centres, or combination of centres, for primary and secondary data (ie, patient characteristics, efficacy endpoints, and safety endpoints) will be made. Continuous data will be presented by descriptive statistics with the number of observations (n), mean, standard deviation, minimum, median, and maximum. Categorical data will be summarized in frequency tables using count and percentages. All tests will be carried out at a significance level of 5% without correction for multiple testing. All patients will be presented in separate data listings. Data from patients screened, but not included in the study, will not be presented in any tables or listings.

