### **8.2.2 Efficacy**

The primary endpoint will be lesion response rate determined by clinical assessment (visual inspection and palpation) 3, 12 and 36 months after Metvix® PDT treatment. Lesion response rate is defined as number of lesions in complete response at the follow-up.

The primary hypothesis to be tested will be:

$$H_0: \mu_1 \leq \mu_2 - \delta_0 \text{ vs. } H_A: \mu_1 > \mu_2 - \delta_0$$

Here  $\mu_1$  = expected response rate for treatment regimen 1,  $\mu_2$  = expected response rate for treatment regimen 2,  $\delta_0 = 0.1$ , non-inferiority margin.

As one patient may yield more than one lesion, a mixed effects logistic regression model with patient identity as random factor will be considered. Different lesions within the same patient will be subject to stratified randomization.

A two-sided 95% confidence interval for difference in lesion response rate will be calculated and supplemented by odds ratio from the logistic regression. The calculation of the confidence interval will be based on data pooled across centers.

Efficacy results will be presented for the ITT and for the PP population.

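### The 170 lesions per group fit only a one-sided 5% test, whereas the one interval planned for the difference is a two-sided 95% interval; if that interval decides non-inferiority, power is about 72-73%, not 80%

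*Protocol*

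**What the plan says.** Three parts of the protocol bear on the error rate of the primary comparison.

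- **Section 8.3 (sample size):** "With a significance level of 5% and a power of 80% a sample size of 170 lesions per group is required". The calculation is attributed to exact software ("ref StatExact 8, Cytel Corp. USA"). The reference assumption is "The cure rate at 3 years with conventional treatment (5, 6) is expected to be 85" per cent, with "i.e. a non-inferiority margin of 10" per cent. Recruitment is raised to 187 per group to allow for loss to follow-up.
- **Section 8.2.2 (efficacy):** after "The primary hypothesis to be tested will be" comes a one-directional non-inferiority hypothesis with a margin of 0.1 and no error rate attached. For the difference itself, the section says: "A two-sided 95% confidence interval for difference in lesion response rate will be calculated". An odds ratio from the logistic regression supplements it.
- **Section 8.2 (general):** "All tests will be carried out at a significance level of 5% without correction for multiple testing".

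None of these sections says whether 5% is one-sided or two-sided. Nowhere does the protocol mention a 90% interval, or say which limit of the 95% interval, if any, settles non-inferiority.

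The synopsis (Statistics) repeats 170 per group, 5% and 80% power beside a different rate: "The expected cure rate at 3 years (reference) is set to 80" per cent. Section 8.2.1 also expects 80%.

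**The concern.** In a non-inferiority comparison the lower limit of a two-sided 95% interval is a one-sided 2.5% test, and the lower limit of a two-sided 90% interval is a one-sided 5% test. The same 5% label can therefore mean two different hurdles. The sample size appears to use the easier hurdle, while the interval written for the difference corresponds to the harder one.

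Two things are at stake. The stated 80% power is a figure the trial relies on, and it is correct under one reading only. The verdict can also depend on the reading: a result may pass a one-sided 5% test while the 95% interval still reaches below -10 points. With no decision rule written down, the choice between them could be made after the result is known.

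**Working it through.** **Inputs.** Cure rate 85% (section 8.3); margin 0.10 (8.2.2, 8.3); equal groups of 170 evaluable or 187 recruited (8.3); target power 80% (8.3). Two assumptions are mine, because the protocol does not state them: the true rates are equal in the two regimes, and lesions are independent.

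**Step 1: reproduce the plan's figure.** The unpooled formula is

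n per group = (z_α + z_β)² × 2p(1 − p) / δ², with z_β = 0.842 and 2p(1 − p) = 2 × 0.85 × 0.15 = 0.255.

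- One-sided 5%: (1.645 + 0.842)² × 0.255 / 0.01 = 157.7, so 158. The score test (variance restricted to the null) gives 163.
- One-sided 2.5%: (1.960 + 0.842)² × 0.255 / 0.01 = 200.1, so 201. The score test gives 207, and an exact unconditional test gives 79.9% power at 207 and 80.8% at 210.

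The stated 170 lies slightly above the one-sided 5% results and at least 31 below the one-sided 2.5% results. Superiority formulas for 85% against 75% do not explain it: they give 197-217 one-sided and 250-270 two-sided. Of the designs tried, only one-sided 5% at 85% is compatible with 170.

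**Step 2: power at the planned sizes, 85% in both regimes.** The normal approximation is Φ(δ/SE − z_α), with SE = √(0.255/n). For n = 170, δ/SE = 0.10/0.03873 = 2.582.

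- One-sided 5%: Φ(2.582 − 1.645) = 82.6%
- One-sided 2.5%: Φ(2.582 − 1.960) = 73.3%

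Checked by binomial enumeration and by an exact unconditional test ordered on the score statistic, as a stand-in for the cited software:

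| Lesions per group | Test | Unpooled, enumerated | Score, enumerated | Exact unconditional |
|---|---|---|---|---|
| 170 | one-sided 5% | 82.6% | 82.0% | 81.3% |
| 170 | one-sided 2.5% (95% interval) | 73.1% | 72.1% | 71.7% |
| 187 | one-sided 2.5% (95% interval) | 77.6% | 76.5% | 75.8% |

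**Step 3: consequence.** If the 95% interval decides, the chance of not showing non-inferiority when both regimes cure 85% is about 27-28% (100 − 73 to 100 − 72), against the 20% implied by the plan. On the score test at 170 per group, 82.0 − 72.1 = 9.9, so about 10% of such trials would pass at one-sided 5% while the 95% interval still included -10 points.

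**Step 4: the synopsis rate.** With 80% in both regimes, 2p(1 − p) = 0.32 and δ/SE at 170 is 2.305. Power is Φ(2.305 − 1.645) = 74.5% at one-sided 5% and Φ(2.305 − 1.960) = 63.5% at one-sided 2.5%. Score enumeration gives 74.6% and 63.2%. The 80% power beside the 80% rate is therefore not reached on either reading.

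**The case against.** The strongest reply is that the decision rule is inferred. Section 8.2.2 says only that the interval will be calculated; it does not make its lower limit the criterion. Read together, the directional hypothesis, the general 5% level in 8.2 and the 5% in 8.3 are consistent with a one-sided 5% test plus a conventional 95% interval reported as an estimate. On that reading 170 is adequate at 85%. This stands, and it makes the shortfall conditional. It does not remove the point, because the only interval named for the difference would then not correspond to the test that decides.

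A reader might go further and infer that the trial is underpowered by its own decision rule, or that the plan would call the same result both a success and a failure. The document does not support that: it contains no interval-based success criterion. That 8.3 used one-sided 5% is likewise a back-calculation, and 158-163 is near 170 but not equal to it.

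The design could also recover some power. Section 4.1 plans 374 lesions in 277 patients, and section 5.2 gives a patient's next lesion the other regime. If no patient has more than two lesions, there are 374 − 277 = 97 opposite-regime pairs. An assumed within-patient correlation of 0, 0.1 or 0.2 then gives about 77%, 79% or 82% power at one-sided 2.5% with all 187 evaluable. With 170 evaluable (about 88 pairs) it gives about 73%, 76% or 78%. This uses SE² = 0.255/n − 2 × pairs × correlation × 0.1275/n², and needs an analysis that exploits the pairing; 8.2.2 says only that the mixed model will be considered. The correlation is unknown, so this does not establish 80%, but any restated power should name the independence assumption.

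Finally, deciding on the 95% interval is the stricter choice, so the false-positive risk is not inflated on that reading.

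**Conclusion.** The point holds in conditional form. The sizing in 8.3 and the interval in 8.2.2 correspond to different error rates, and the protocol does not say which one governs. If the two-sided 95% interval decides, power is about 72-73% with 170 evaluable lesions per group, a shortfall of 7-8 points from the stated 80%. With no losses at all (187 per group) it is about 76-78%, so the recruitment allowance does not close the gap. If a one-sided 5% test decides, power is about 81-83% and the matching interval is 90%.

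These figures assume 85% cure in both regimes, a 10-point margin and independent lesions. The arithmetic is firm; which reading the sponsor intends is not determined by the document. Both readings need a correction.

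**What to change.** State one error rate and one decision rule in section 8.2.2, before outcomes are compared by regime. Either:

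- **(a)** conclude non-inferiority if the lower limit of the two-sided 95% interval for regime 1 minus regime 2 exceeds -10 percentage points, and restate the power in 8.3 as about 72-73% with 170 evaluable lesions per group (85% cure rate, one-sided 2.5%, independent lesions); or
- **(b)** state one-sided 5% in 8.3 and make the interval in 8.2.2 a two-sided 90% interval.

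Do not carry 72-73% into the synopsis while it uses an 80% reference rate. First reconcile the 80% in the synopsis and section 8.2.1 with the 85% in 8.3, then give the matching power in both places.

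The cost is wording in 8.2.2, 8.3 and the synopsis, plus 8.2.1 if its rate changes. No extra patients are needed. The downside is a less favourable stated power under (a), or a more lenient error rate under (b).
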